### Self-regulation

As mentioned above, SR skills were divided in basal and complex SR sub-facets.

#### Basal SR sub-facets

Basal SR sub-facets include inhibition, working-memory updating, cognitive flexibility, heart rate variability (HRV), and emotional reactivity. Inhibition, cognitive flexibility and emotional reactivity are collected online, while the HRV and working-memory updating are collected in the face-to-face on site assessment.

##### Inhibition

The ability to control, modulate, and plan one’s behavior, to suppress primary behavioral impulses and inappropriate responses, and to resist impulsive behavior was assessed at T1–T3 via parent-ratings with six items from the Inhibitory Control subscale of the Temperament in Middle Childhood Questionnaire [43]. The ability to suppress primary behavioral impulses in favor of a less dominant response was also assessed with a performance-based measure at T1–T3 using an adaptation of the Fruit-Stroop Task [44, 45]. At T4, an age-appropriate computer-based Stroop Task is used [46]. Against a black background, participants see a color word (RED, BLUE, GREEN) printed in different colors (red, blue, green). After the color word appears, the participants have to name the ink-color as quickly as possible. The first 42 trials are performed without response conflicts (words replaced by rows of three to five asterisks), followed by runs with color words. The initial 42 color words are presented with congruent ink, and the following 42 words with incongruent ink, which requires the inhibition of a predominant response (e.g., reading the color word) to correctly name the ink-color. Inhibition capacities are measured via interference scores calculated from reaction times or accuracy in congruent relative to incongruent trials. Preceding the Stroop test at T4, potential color-vision deficiency is assessed via self-report with two self-constructed items: whether the adolescent is struggling with identifying colors and, if applicable, from which color-vision deficiency they are suffering.

##### Working-memory updating

At T1–T3, the ability to actively monitor and manipulate information in short-term memory was assessed using the Digit Span Backward (ZN-R) subtest of the German version of the Wechsler Intelligence Scale for Children—Fourth Edition (WISC-IV; 6–16 years; [47]). At T4, the corresponding subtest of the Wechsler Adult Intelligence scale—Fourth Edition (WAIS-IV; from 16 years; [48]) as an age-appropriate version is used. The participants hear a series of individual spoken digits and are asked to verbally repeat the digits in reverse order. After a correct repetition, the following series is extended by one digit, and after two incorrect turns, the test is terminated. The measure for updating capacity is the length of the final sequence or the number of sequences repeated correctly in reversed order.

##### Cognitive flexibility

The ability to adjust the attentional focus to current demands or to flexibly shift between mental sets and demands was assessed via the child-appropriate, performance-based Cognitive Flexibility Task [49] at T1 and T2. From T3 onwards, the age-appropriate performance-based Dimensional Change Card Sorting (DCCS) task is being used [50]: On a computer screen, participants are presented with two geometrical symbols that vary across the two dimensions ‘shape’ and ‘color’ (i.e., a blue box and yellow star). A third symbol with complimentary features (i.e., blue star) must then be matched as quickly as possible to one of the two original shapes via keypress according to a fixed rule indicted by a verbal cue (i.e., ‘shape’ or ‘color’). The 20 trials of the first block establish a dominant rule (i.e., 50% of participants sort by shape or color, respectively). In the second block, trials appear in pseudo-random order: 45 non-switch trials follow the dominant rule and 15 switch trials require the other, non-dominant rule. There is always at least one dominant trial between two non-dominant trials. The costs of switching to the new sorting rule are calculated from reaction times or accuracy in the switch relative to the non-switch trials. High cognitive flexibility comes with low switch costs.

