### Study measures

The PIER-study already included multiple measures of SR as self-reports, parent- and teacher-reports, and performance-based computer tasks. On a construct level, these assessments and objective measures continue in PIER_YOUTH_, although sometimes the specific assessment procedure had to be adjusted to the older age of the participants. In the following, not only the assessments at T4 will be described, but also the corresponding assessments at T1–T3 in order to clarify necessary age-dependent adjustments. An overview of the study measures is presented in Table 2. Of note, the questionnaires and performance-based tasks are presented to the participants in a block-randomized sequence in order to control for order effects (4 blocks). The computer tasks were programmed in E-Prime 2.0 Professional (2012 Psychology Software Tools) at T1–T3 and in JATOS/OpenSesame at T4. Online questionnaires were programmed with SoSci Survey (version 3.4).

**Table 2 Tab2:** Overview of the measurement instruments across the measurement time points as well as reporting source

Construct	Measurement	Measurement time			
		T1	T2	T3	T4
*Basal self-regulation sub-facets*					
Inhibition	Fruit-Stroop task	PB	PB	PB	
	Stroop task				PB
	Control variables for Stoop task: items about color weakness/blindness				S
	Subscale inhibitory control of the temperament in middle childhood questionnaire (TMCQ)	P	P	P	
Working-memory updating	Digit Span Backward (ZN-R) subtest of German Wechsler Intelligence Scale for Children—Fourth Edition (WISC-IV)/Wechsler Adult Intelligence Scale—Fourth Edition (WAIS-IV) [age-appropriate version]	PB	PB	PB	PB
Cognitive flexibility	Cognitive flexibility task	PB	PB		
	Dimensional change card sorting (DCCS) [age-appropriate version]			PB	PB
Heart rate variability (HRV)	Polar watches (RS800CX, Polar Electro Oy, Kempele)	O	O		
	BioSign HRV-scanner				O
	Control variables for HRV: Questions about variables that might affect HRV-measurement: consume of caffeine/cardioactive substances; in-tensive physical training during the last 24 h; sleep quality and duration of the previous night; time of the last meal				S
Emotional reactivity	Subscale emotional control of the behavior rating inventory of executive function (BRIEF)	P	P	P	S, P
	Subscale anger/frustration of the temperament in middle childhood questionnaire (TMCQ)	P	P		
	Subscale anger of the Buss-Perry-aggression questionnaire				S
*Complex self-regulation sub-facets*					

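### The card-sorting switch cost is aliased with sorting dimension within each participant, so any average shape-colour difference shifts individual scores in opposite directions in the two halves of the sample

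*Protocol article*

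**What the plan says.** The Cognitive flexibility section of the protocol article (under Basal SR sub-facets) describes the DCCS task used from T3 onwards. On the first block it says: "The 20 trials of the first block establish a dominant rule (i.e., 50% of participants sort by shape or color, respectively". On the second, scored block it says: "45 non-switch trials follow the dominant rule and 15 switch trials require the other, non-dominant rule". The score is defined by: "The costs of switching to the new sorting rule are calculated from reaction times or accuracy in the switch relative to the non-switch trials". It is read at the level of the person: "High cognitive flexibility comes with low switch costs".

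Table 2 lists the DCCS as the only cognitive-flexibility measure at T3 and T4. The Statistical analyses section plans latent factors, cross-lagged models and latent-growth models, and mentions method factors for rater effects. Nothing in the article uses the dominant dimension in scoring or analysis.

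**The concern.** A switch cost should compare the same kind of sorting with and without a change of rule. Here no participant provides that comparison. Someone whose dominant rule is colour does all non-switch trials by colour and all switch trials by shape; for someone whose dominant rule is shape it is the reverse. Within a person, the cost of switching and the difference between the two dimensions cannot be separated.

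Splitting the dominant rule 50:50 is a sound device when the target is a group mean. This study instead relates each person's score to other facets and outcomes. If the dimensions differ in difficulty, two equally flexible participants receive different scores because of the version they were given. At stake are attenuated associations wherever the DCCS score stands alone for cognitive flexibility, and a possible distortion of its T3-T4 stability.

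**Working it through.** The plan gives no figure on this point to reproduce, so the check is algebra plus a range of assumed sizes.

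**Inputs from the article.** 45 non-switch trials, all on the dominant dimension; 15 switch trials, all on the other; half the participants with each dominant dimension (Cognitive flexibility). N = 1074 at T4 and a smallest cross-lagged effect of r = 0.09 (Power analysis).

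**Assumed, because not in the article.** d = mean time to sort by shape minus mean time to sort by colour; k = d/SD of the true switch cost, taken as 0.25, 0.50 and 0.75; a reliability of 0.60 for the illustration with measurement error.

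**Difference score.** With true cost S:
- colour dominant: (colour + d + S) - colour = S + d
- shape dominant: (shape - d + S) - shape = S - d

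Example: S = 100 ms and d = 50 ms give 150 and 50 ms. The mean over equal halves is 100 ms, which is correct, but the halves are 2d = 100 ms apart. With d = 0 both score 100 ms.

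**Ratio score.** If the shape-to-colour time ratio is q and switching multiplies time by s, the halves score s × q and s / q. The shift is multiplicative and again opposite in direction.

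**Share of score variance due to version.** With SD(S) = 1, version contributes k². Without measurement error the share is k²/(1 + k²) and associations are multiplied by 1/√(1 + k²). With reliability 0.60 before version is added, error variance is 1/0.60 - 1 = 0.667. The share becomes k²/(1.667 + k²) and the added attenuation √(1.667/(1.667 + k²)).

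| k | Share, no error | Attenuation | 0.09 becomes | Share, reliability 0.60 | Added attenuation |
|---|---|---|---|---|---|
| 0 | 0% | 1.00 | 0.090 | 0% | 1.00 |
| 0.25 | 5.9% | 0.97 | 0.087 | 3.6% | 0.98 |
| 0.50 | 20% | 0.89 | 0.080 | 13% | 0.93 |
| 0.75 | 36% | 0.80 | 0.072 | 25% | 0.86 |

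For scale only, the Fisher-z power of a simple correlation at N = 1074 (two-sided 5%) is 0.84 at r = 0.09. It falls to 0.82, 0.75 and 0.66 for the three error-free values. This is not the article's cross-lagged simulation.

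**T3-T4 stability.** Suppose a true stability of 0.40, k = 0.50 at both waves and no error. If participants keep their version, the observed value is (0.40 + 0.25)/1.25 = 0.52. If version is drawn anew, it is 0.40/1.25 = 0.32. The article does not say which applies.

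**What adjustment recovers.** A simulation of 400,000 persons with d = 0.50 and a person-to-person SD of the shape-colour difference of 0.25 (both in units of SD(S), no other error) gave a correlation between score and true cost of 0.87 raw and 0.97 after centring within version. The remainder is person-specific and cannot be removed.

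**Trial order does not change this.** The article adds: "There is always at least one dominant trial between two non-dominant trials". That affects which trials form the baseline, a separate matter; the whole baseline stays on the dominant dimension.

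**The case against.** The strongest reply is that a journal article condenses the plan. Indicator-level scoring and nuisance covariates often sit in a full protocol or SAP, which is not shown, and the article does not rule out adjusting for version. It even leaves open reaction time or accuracy, and difference or ratio. This stands to the extent that a missing covariate is not in itself an error. It does not dispose of the point, because the scoring rule that is stated yields version-dependent individual scores whenever d is not zero. The article also names control variables for the Stroop task and for heart rate variability in Table 2, but none for the DCCS.

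A second reply is that latent modelling absorbs the problem. That is right in part. Where several different measures define a factor, variance unique to the DCCS goes into its residual. It gives no protection where the DCCS is the sole indicator, and parcels of its own trials would all carry the same offset.

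Some stronger readings are tempting but not supported:
- A reader might infer that every score is wrong by plus or minus the shape-colour difference. That needs a non-zero d, which the article neither gives nor implies, and a difference score.
- A reader might take the halves as randomised. The article states only a 50% split. The randomisation it describes concerns the order of instruments: "the questionnaires and performance-based tasks are presented to the participants in a block-randomized sequence in order to control for order effects (4 blocks".
- A reader might take the error-free variance shares as expected sizes. A cost resting on 15 switch trials will carry measurement error, which lowers them.
- A reader might conclude that stability is inflated, or deflated. Both figures rest on assumed values and on an unstated allocation of versions between waves.

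**Conclusion.** The aliasing of switching with dimension follows directly from the task description. Under the stated scoring rule, an average shape-colour difference enters individual scores with opposite sign in the two halves. The even split protects the overall mean but not the individual-differences analyses.

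The consequence is conditional and its size unknown. At k = 0.25 it is negligible: r moves from 0.090 to 0.087 even without error. At k = 0.75 without error it is material, with 36% of score variance due to version. These values rest on an assumed d, and the attenuation applies where the DCCS score is used alone. Stability may be biased in either direction. This is an inexpensive improvement to the scoring, not an error that invalidates the planned analyses.

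**What to change.** In the Cognitive flexibility section, add one sentence: the switch cost is centred on the mean of the participant's dominant-rule version at each wave, or dominant dimension (shape or colour) enters as a covariate on the DCCS indicator at T3 and T4. Report the version mean difference at each wave, and say how versions were assigned and whether participants keep theirs from T3 to T4. If the halves are comparable, the version mean difference estimates 2d, and the T3 data already collected can show now whether d is near zero.

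The cost is one binary covariate that the task already assigns, provided it was recorded: one degree of freedom per wave and no new data. Two limits remain. Person-specific shape-colour differences stay in the score. If the halves are not comparable, centring would also remove any true difference in flexibility between them.

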##### Heart rate variability (HRV)

HRV, as a measure of neurovegetative activity and autonomic function of the heart, characterizes variations in heart rate over a given measurement period. High HRV is considered a biological marker of good self-regulatory capacity [51, 52]. HRV was collected at T1 and T2 using electrodes on the palms of the hands for a period of 3 min using Polar watches (RS800CX, Polar Electro Oy, Kempele) [53]. From T4 onwards, the heart rate is being objectively measured using clamp electrodes applied on the participants’ wrists and the software BioSign HRV-Scanner standard professional version 3.5 [54] for a period of 5 min. Furthermore, a number of external factors that may influence HRV are assessed as self-report. With self-constructed items, adolescents indicate whether they have (1) consumed caffeine in the previous 2 h, (2) consumed other cardioactive substances (such as nicotine, alcohol, other drugs) or undergone intensive physical training during the last 24 h. Moreover, three open questions are used to assess the quality and duration of sleep during the previous night, and the time of the last meal.

##### Emotional reactivity

The tendency to show strong emotional reactions in general was recorded at T1–T3 with the subscale *emotional control* of the Behavior Rating Inventory of Executive Function (BRIEF; [55]) via parent-report. From T4 onwards, the same scale is used to assess emotional reactivity via self- and parent-report. The proneness to react with anger in the face of interruption of tasks or hindrance in goal achievement in particular was recorded at T1 and T2 using seven items of the Anger/Frustration subscale of the Temperament in Middle Childhood Questionnaire (TMCQ; [43]) via parent-report. From T4 onwards, anger reactivity is assessed as self-report via six items (as suggested by [56]) of the *Anger* subscale of the Buss-Perry Aggression Questionnaire (German: [56]).

#### Complex SR sub-facets

Complex SR sub-facets include emotion regulation strategies, affective decision making, delay of gratification, risk-taking/impulsivity, planning behavior, conscientiousness, and eating-related SR. All these assessments are conducted during the online session.

##### Emotion regulation strategies

At T1–T3, anger-regulation strategies (dispersion, perseveration, expression, control, external regulation) were recorded via age-appropriately adapted items of the Dealing with Anger subscale of the Questionnaire to Elicit Emotion Regulation in Children and Adolescents (FEEL-KJ; [57]) via self- and parent-reports. Furthermore, at T1 and T2 strategies of dealing with anger were assessed via an adaption of the Emotion Regulation subscale of the Intelligence and Development Scales (IDS; [58]) via self-reports. At T4, the German versions of the Emotion Regulation Questionnaire (ERQ; [59]) and the 27-item version of the Cognitive Emotion Regulation Questionnaire (CERQ; [60]) are used to capture self-reported emotion-regulation strategies, namely cognitive reappraisal and expressive suppression (ERQ) as well as “functional” (e.g., relativizing, refocusing) and “dysfunctional” (e.g., self-blame, rumination) strategies (CERQ).

##### Affective decision-making

The tendency to make emotion-driven decisions and take risks was assessed at T1–T3 using the computer-based Hungry Donkey Task [61]. At T4, we use an age-appropriate version with a higher number of trials and a more complex pattern of win-loss probabilities [62]. Participants are asked to help a hungry donkey and to collect as many apples as possible by selecting and opening one of four depicted doors in 100 trials. After opening a door, certain numbers of gained (green) and lost (red) apples are displayed (e.g., + 4, − 8). The exact win-loss probability is different for each door and unknown to the participants. Relevant measures are the number of apples obtained (net gain) or the difference of choices for “disadvantageous” door positions (yielding higher immediate gains but long-term losses) versus “advantageous” door positions (yielding lower immediate gains but long-term gains) across trials (e.g., all trials or in learning blocks with several trials each). A preference for disadvantageous doors reflects poorer affective decision making, a preference for immediate rewards, or a stronger insensitivity to negative consequences.

##### Delay of gratification

The ability to forgo an immediate reward and to control impulses in favor of a larger or higher value in the future was assessed at T1–T3 using four decision questions [63]. Children needed to decide whether they wanted to obtain a smaller amount of real incentives (2 sweets, 2 toys) immediately or a larger amount some time later. At T4, the German Delay Discounting Test (DDT; [64, 65]) is used. In 27 items, participants are asked to imagine they would receive money from the test administrator, and they must choose between a smaller, immediate amount of money or a larger amount of money to be received later. The derived discount rate informs on how much a person devalues a future reward (referred to as delay discounting). The discount rate depends, among other variables, on the value of the immediately available reward and the delay interval. A low devaluation of future rewards speaks for higher delay-of-gratification ability.

##### Behavioral control/impulsivity

At T4, this facet is assessed via self- and parent-reports, using a short version of the UPPS Impulsive Behavior Scale (UPPS; adapted from [66] and [67]; 10 items on four subscales: lack of premediation, urgency, sensation seeking, and (lack of) perseverance) and the Self-Regulation Scale (SRS, 10 items; [68]). The SRS captures the ability to sustain difficult actions even when attention or motivation is impaired. Furthermore, at T4, risk-taking is assessed using the computer-based Balloon Analogue Risk Task [69] as a behavioral measure with 20 trials. The task consists of inflating a balloon displayed on a computer screen by pressing a button repeatedly, with each press yielding a small monetary reward (0.5 Cent) that the participants actually receive after the test session. After each key press, participants have to decide either to continue inflating the balloon and thus increase their monetary reward, or to stop inflating it. With further inflation, participants increase the risk that the balloon will burst (in which case all money of this trial is lost), whereas termination secures the money earned in this trial. As dependent variable the so-called adjusted average pumps, i.e., pumps on the balloons which did not explode, will be calculated.

##### Planning behavior

At T1–T3, the child’s ability to deal with tasks that have to be mastered now or in the future was measured via teacher-reports with the Plan/Organize subscale of the BRIEF [55]. At T4, this subscale is included as a self- and parent-report. Additionally, planning behavior is assessed with the two Intention-items of the UPPS (adapted from [66, 67]) described above. Furthermore, five items of the Impulsivity subscale from the German version of the Barratt Impulsiveness Scale (BIS) (German: [70]) are assessed via self-report.

##### Conscientiousness

Conscientiousness, one of the personality dimensions of the Big Five, is considered as self-regulatory competence in personality psychology [71]. Conscientiousness refers to the tendency to be disciplined, perform well, and be reliable. At T4, it is assessed using parsimonious subscale of a short version the Big Five Inventory-SOEP (BFI-S; [72]) via self-report (3 items).

##### Eating-related SR

SR competencies associated with eating behavior that are regarded as contributing to weight status were assessed at T1–T3. The emotional overeating, emotional undereating, food responsiveness, and satiety responsiveness subscales of the Children’s Eating Behavior Questionnaire were assessed via parent-report (CEBQ; [73]). Moreover, at T3, a short version of the restrictive eating behavior subscale of the Dutch Eating Behavior Questionnaire for children (DEBQ; [74]) and six items of the Eating Behavior Disturbance Questionnaire [75] assessing emotional eating were used (self-reports). Furthermore, the subscale external eating behavior of the DEBQ [75] was assessed via parent-report. At T4, the CEBQ is assessed via parent-report, and the German version of the Adult Eating Behavior Questionnaire (AEBQ; [76, 77]) is applied as self-report. An age-appropriate version of the DEBQ is used to assess restrictive eating behavior via self-report and external eating behavior via parent-report [78]. Furthermore, the survey is assessing food self-regulation via self-report. On two self-constructed slider scales, the participants are indicating their determination of losing weight and changing eating behaviors in the near future.

